### Outcome measures

The current study investigates the effect of aqua-cycling on impairments due to knee OA, such as knee pain, reduced physical functioning over the previous week and on the assessment day, and knee stiffness. It also seeks to make an overall assessment of disease severity and lower limb muscle strength compared with a control group receiving usual care.

Furthermore, the phenomenon of aqua-cycling is explored in a more general health context through evaluating the effect of aqua-cycling on functional capacity, physical activity level and quality of life. Psychological measures on self-efficacy and fear of movement are also assessed. Outcomes are assessed in person, but to keep the number of missing values as small as possible, all questionnaires will be sent by mail to any participants unable to come to the MUMC^+^. An overview of all measures and timing of assessment is given in Table 2.

**Table 2 Tab2:**
[figure not shown]
Overview of measures and timing of assessment

#### Primary outcome

The self-reported score on knee pain and physical functioning assessed with the *Knee Injury and Osteoarthritis Outcome Score* (KOOS*,*http://www.koos.nu) is the primary outcome measure. The KOOS questionnaire is an extended version of the Western Ontario and McMaster Universities Arthritis Index (WOMAC), which is a well-recognised, valid and responsible outcome measure in knee OA research [48]. In addition to the WOMAC subscales for pain, stiffness and physical function (in its complete and original format), the KOOS also takes into account difficulties with sport activities and knee-related quality of life. The five subscales are scored on a five-point Likert scale and final scores are modified to a 0–100 scale. A lower score is associated with higher impairments. The Dutch KOOS shows good, internal validity (Cronbach’s α: 0.71), construct validity (Spearman correlation between KOOS subscales and SF-36 pain and physical function: 0.63, 0.75) and is a reliable (ICC: 0.45-0.89) measurement for patients with mild to moderate knee OA [49]. The KOOS is self-administered and patients need approximately 10 min to answer all questions [50].

#### Secondary outcomes

The *Lower Extremity Function Scale (LEFS)* is a patient-reported measure on physical functioning on the test day [51]. The questionnaire consists of 20 questions and patients can complete it within a few minutes. The Dutch version of the LEFS has favourable psychometric properties: good internal consistency (0.96), reliability (ICC = 0.86) and a good construct and discriminant validity [52]. It is a disease-specific questionnaire and each item is scored on a five-point Likert scale. The total score ranges from 0 to 80 points. A higher score is associated with better physical functioning.

*Numeric pain rating scales (NPRS)* are frequently used to assess pain intensity in OA and the NPRS has been recommended as a core outcome measure for chronic pain trials [53, 54]. Previous research showed that the NPRS is a valid and responsive tool for pain measurements in OA patients and also a reliable tool (ICC: 0.64 to 0.86) in patients with orthopaedic problems and musculoskeletal pain [55, 56]. The NPRS is a self-administered scale, completed in less than 1 min and a lower score indicates less pain.

Osteoarthritis research societies have defined a core set of outcome measures for clinical OA trials: pain, function and *Patient Global Assessment* (PGA) [57]. Participants will be asked to consider all the ways in which illness and health conditions are affecting them at the time of the assessment and to mark one of 21 numbered circles on a visual analogue scale (VAS) [58]. A higher scores means that the participant feels more affected by their illness and health conditions. The PGA has a good test-retest reliability (ICC: 0.702) in patients with rheumatic arthritis and is completed by patients within a few seconds [58].

Data on *isometric and isokinetic muscle strength* of hamstring and quadriceps of the affected leg are collected with the dynamometer Biodex® System 3 Pro. The isometric quadriceps and hamstring muscle strength are tested in 30° and 60° fixation with three repetitions each. Isokinetic quadriceps and hamstring muscle strength are measured at 60° per second (five repetitions) and 180° degrees per second (five repetitions). The reliability of isometric and isokinetic strength testing is moderate (r = 0.8–0.9) to high (r > 0.9) in patients with mild knee OA [59].

The *Timed up and Go (TUG)* performance test measures the time needed by a patient to get out of a chair, walk three metres, return and get back into the chair. The guideline for physical therapy in patients with hip and knee OA of the Royal Dutch Society for Physical Therapy recommends the use of the TUG in combination with questionnaires (e.g. KOOS) to evaluate treatment goals for physical functioning [60, 61]. The inter-rater reliability between three physical therapists assessing patients with rheumatoid arthritis was high (ICC: 0.97) [62]. Intra-session reliability was also satisfactory: ICC of 0.75 with a time interval of more than 25 weeks and an ICC of 0.87 with a time interval of less than 1 week [63, 64]. In frail elderly patients and elderly patients undergoing orthopaedic rehabilitation, the TUG correlates well with gait speed (r = -0.61, 0.745) and performance of day-to-day activities (r = -0.78) and correlates highly with the Berg Balance Scale (r = -0.81) [65, 66].

The *6-Min-Walking-Test (6MWT)* is a simple test, recommended by the Dutch physical therapy guideline for OA, to assess functional capacity [61, 67]. Over a period of 6 min, participants walk at a self-chosen speed with the aim of covering as much ground as possible. Participants have to walk in a square with a total length of 44 metres. This set-up deviates from the standard as recommended by the American Thoracic Society which includes a 30 metre corridor or walkway with cones placed at the beginning and end of the 30-metre boundary to indicate turns [68]. In patients with fibromyalgia and those recovering from total hip and knee surgery, the 6MWT is a reliable test with an ICC for test-retest reliability of 0.94 and 0.98 [63, 69]. In terms of validity, the oxygen uptake during the 6MWT shows a high correlation with peak oxygen uptake values (r = 0.86) obtained during maximum exercise testing in patients with heart failure [70].

The *Short QUestionnaire to ASsess Health-enhancing physical activity (SQUASH)* is a survey to assess habitual physical activity and consists of eleven questions on physical activity in four different contexts: commuting, leisure time, during work and household activities. It is a short and simple questionnaire with proper reliability and validity [71]. The SQUASH is used to evaluate adherence to the Dutch physical activity guideline, recommending 30 min or more of at least moderate intense physical activity for a minimum of 5 days per week [72]. With regard to OA, only one study evaluated the SQUASH. Wagenmakers et al. found a good correlation with an accelerometer (r = 0.56) in patients with hip OA after surgery [73].

The *Rand 36-item Health Survey* (Rand-36) is a generic tool to measure health-related quality of life (HRQoL) [74]. It consists of 36 items that cover eight HRQoL domains: physical functioning, role limitations because of physical health problems, bodily pain, general health perception, vitality, social functioning, role limitations because of emotional problems, and mental health. The total score ranges from 0–100, with a higher score indicating better health status. The Rand-36 is almost identical to the Medical Outcome Study (MOS) Short-Form-36 (SF-36), and both have a proven sound responsiveness in patients with knee OA (SRM = 0.528), and internal consistency (Cronbach’s α: > 0.70) and test-retest reliability (ICC: 0.40-0.82) in a Dutch general population [75–79].

The *Tampa Scale for Kinesiophobia (TSK)* is used to assess fear of injury/re-injury due to movement [80]. It is a 17-item scale that is scored on a four-point scale from ‘strongly disagree’ to ‘strongly agree’. The present study uses the Dutch version which shows good psychometric properties in patients with acute low back pain: good internal consistency (Cronbach’s alpha = 0.70) and satisfactory test-retest reliability (ICC: 0.76) [81].

The *Arthritis Self-Efficacy Scale (ASES)* is a valid and responsible measure providing information on patients’ self-efficacy to perform a task (e.g. ‘How certain are you that you can walk 100 feet on flat ground in 20 seconds?’) or to achieve a specific behaviour (e.g. ‘How certain are you that you can decrease your pain quite a bit?’) [82, 83]. In total, the scale consists of 20 items that are divided into three subscales: self-efficacy pain scale, self-efficacy function scale and self-efficacy other symptoms scale (e.g. fatigues, enjoyment). The items are scored on a ten-point Likert scale resulting in a total score ranging from 0 to 100. Higher scores indicate a better self-efficacy. The ASES has been translated and is available in Dutch [84]. The present study measures the self-efficacy for function. This subscale has a good test-retest reliability (ICC: 0.85) and internal consistency (Cronbach’s alpha = 0.89) [85].

#### Process measures

*Daily diaries* collect information on knee pain, physical functioning, level of physical activity, pain medication routine and physical therapy participation over two 30-day periods (during the intervention period). Participants can fill in the diaries on a computer or in a printed booklet version. Information on physical functioning and physical activity is gathered by questions derived from the LEFS and SQUASH questionnaires [52, 72]. Knee pain is measured by NPRS [55]. The section on medication use asks if pain medication is used for knee pain or other pain, the name of the pain medication and the dosage and time-point(s) of taking the medication. Participation in, duration and intensity of exercise routines or physical therapy will be documented as well. Furthermore, four questions, derived from the RAND-36 questionnaire, will ask about the restrictions in physical role functioning. Previous research only shed light on the level of hindrance and/or avoidance of activities, but not on the type of hindrance [86]. The daily repeated measures will provide more insight into the course of pain, physical functioning, physical activity and medication use. The diary data from the intervention group will yield important information on the development of impairments, level of physical activity and medication use in response to the aqua-cycling programme. The diaries of the control group will provide a picture of the level of physical activity, participation in exercise therapy and the development of impairments over time. Previous research using booklet diaries and comparable diary periods showed good compliance and a low dropout rate, indicating that this method is acceptable for chronic pain patients [87].

*Participants’ experience with aqua-cycling* will be assessed after the final training session by means of planned focus-group sessions. Small-group interviews will be planned, and participants will be asked broad, open-ended questions about their expectations, fulfilment of expectations, positive and negative aspects of the training and suggestions for further development of the training. Thirty per cent of the participants (~20 participants) in the intervention group will be invited to attend small-group interviews to provide feedback.

*Attendance, adverse events and exercise progression of the intervention group * were registered by the physical therapist. For every patient a training log book exists where the physical therapist documented date and number of the training sessions attended. In total every patient could attend 24 sessions. Pedalling tempo and resistance, heart rate and BORG scores were noted for every exercise during the conditioning phase. Furthermore, the physical therapist documented the occurrence and type of problems with the performance of certain exercises in an indicated open text box in the training logbook. Thus, the physical therapist described the type of problem, whether the participants were able to continue the exercise and in case of performance restrictions the alternative exercise was described. Also, adverse effects during or following the sessions were documented in the training log book. Non-serious adverse effects were defined as increased joint pain, stiffness, muscle soreness and/or fatigue occurring during or immediately after the last training session [88, 89]. If these adverse events were experienced longer than 24-h or interfered with physical activities and social participation they were classified as severe adverse events [89]. A serious adverse event was defined as an occurrence that resulted in permanent or severe disability, hospitalization, or death [90].

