All participants were instructed to maintain their usual care routine. The programme coordinator kept track of changes in participants’ treatment plans by monitoring patients with diaries that recorded OA-related functional problems, knee pain, physical activity, physical therapy and medication use in the first and third month after baseline assessment. Furthermore, a short interview by phone (control group) or in person (intervention group) was scheduled after 6 weeks. Prior to the last assessment, the programme coordinator called participants and inquired about any changes in treatment.

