### Data monitoring

The content of the aqua-cycling intervention is comparable to existing physical activity programmes on land. Research has shown that these programmes involve no additional harm or risk to the patient [47, 95]. Aqua-cycling in rheumatic patients was evaluated in a study as safe and feasible [23]. In addition, there is adequate evidence that aquatic training and stationary cycling are beneficial and safe activities for patients with knee OA [14, 19, 20].

Because the risk of any adverse events from participation in the intervention group is small and comparable to the very low risk of adverse events from participation in land-based OA exercise programmes [47], no data monitoring committee (DMC) is needed. In case of a serious adverse event, the programme coordinator will inform all professionals involved in the study and report the event via a web portal to the accredited Medical Ethics Board within 24 h.

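### Adverse events are defined and registered only in the aqua-cycling arm, so their rates have no usual-care comparator, and the diaries kept in both arms fill the gap only in part

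*Protocol article*

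**What the plan says.** Under Process measures, the therapist registers attendance together with "adverse events and exercise progression of the intervention group". The instrument is the session record: "adverse effects during or following the sessions were documented in the training log book". Three grades are defined there:

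- Non-serious: "increased joint pain, stiffness, muscle soreness and/or fatigue occurring during or immediately after the last training session".
- Severe, built on the first grade: "If these adverse events were experienced longer than 24-h or interfered with physical activities and social participation they were classified as severe adverse events".
- Serious: permanent or severe disability, hospitalisation or death, with no link to a session.

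No register and no non-serious or severe definition is given for usual care. Data monitoring covers serious events without limiting them to one arm ("In case of a serious adverse event, the programme coordinator will inform all professionals involved in the study"), but does not say how they would come to light in controls. The same section dispenses with a data monitoring committee because "the risk of any adverse events from participation in the intervention group is small".

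Some information does come from both arms. Participants keep daily diaries in the first and third month, with knee pain on the NPRS, functioning, role restriction and pain medication. Under Both groups, "a short interview by phone (control group) or in person (intervention group) was scheduled after 6 weeks", and the programme coordinator calls before the last assessment to ask about treatment changes. Data analysis plans between-group comparisons of change in diary knee pain and medication use.

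**The concern.** Increased joint pain and stiffness are symptoms of the disease under study, and patients enter with knee pain of four to seven. Some will have bad days after a session that they would have had anyway. Without a control rate, a given log count cannot be called high or low. It may overstate harm by including background symptoms, or a low count may be read as showing safety when nothing was compared.

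The article gives its own reasons to want a comparison. In the Intervention group section it assumes that aqua-cycling demands more than land cycling, acknowledges that evidence is lacking on how body position in aqua-cycling affects knee load, and links higher workload to higher knee load and worse pain. The low-risk argument under Data monitoring rests largely on land-based programmes and other aquatic or cycling studies. This trial's own controlled data could test that argument, but the log cannot.

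Two further features weaken the log. It is kept by the therapist who supervises the sessions, so events are not assessed blind to allocation. It is also tied to attendance: a participant who stops coming because of pain may leave no later entry. That last point is an inference, not something the article states.

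**Working it through.** The plan states no figure for adverse events, so there is none to reproduce. The check sets the definitions beside the data each arm supplies, then asks how far the diaries can substitute.

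**Step 1: can a control patient be counted?** I read the last session in the definition as the most recent one.

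| Category | Needs a training session? | Possible in usual care? |
|---|---|---|
| Non-serious | Yes, by definition | No |
| Severe | Yes, as a subset of the same events | No |
| Serious | No | Yes, but no method of ascertainment stated |

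The rate in controls is therefore undefined for the first two categories. It is not an observed zero.

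**Step 2: how much do the diaries cover?** Inputs: two 30-day periods (Process measures), a 12-week programme and a 24-week trial.

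- Intervention period: 12 × 7 = 84 days; 2 × 30 = 60 diary days; 60/84 = 71%.
- Whole trial: 24 × 7 = 168 days; 60/168 = 36%.
- Not covered: the second month and all of weeks 13 to 24.
- Content: knee pain, functioning, activity, role restriction and medication are listed. Stiffness, muscle soreness and fatigue, three of the four symptoms in the non-serious definition, are not.

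**Step 3: what would a diary flare comparison deliver?** From Sample size, 168 participants with 20% dropout gives 168 × 0.80 / 2 = 67.2, taken as 67 per arm. This assumes that the target was reached and the diaries are usable. The flare proportion p is not in the article, so I assume a range, equal in both arms. The 95% CI half-width is 1.96 × √(2p(1 − p)/67).

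| Assumed p | Half-width (percentage points) |
|---|---|
| 0.10 | 10.2 |
| 0.20 | 13.5 |
| 0.30 | 15.5 |
| 0.40 | 16.6 |

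Power with 67 per arm at two-sided 5%, for assumed proportions: 10% against 30%, 0.83; 20% against 40%, 0.72; 30% against 50%, 0.66; 30% against 55%, 0.84. A flare comparison would bound a large excess but could not exclude a moderate one.

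**Step 4: what can still be changed?** Trial status has data collection ending in March 2016. Counting 24 weeks (168 days) back from 31 March 2016 gives 15 October 2015 as roughly the last baseline date, consistent with recruitment closing that month. Six weeks (42 days) later is 26 November 2015. Six-week interviews are thus largely past. Existing diaries and some final calls are what remain.

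**The case against.** **The diaries already answer the question.** A reader might infer from the one-arm log that the trial can say nothing about whether aqua-cycling provokes more pain flares than usual care. The documents do not support that. Both arms record daily NPRS pain, a between-group comparison of change is planned, and KOOS is taken in both arms at baseline, 12 and 24 weeks. This objection stands against the strong reading. It does not remove the point: an average course can improve while some participants have short, marked worsenings, no flare rule is stated, and the coverage limits in Step 2 remain.

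**The log does not count every flare.** A reader might also infer that all background flares will be booked as programme harms and set against none in controls. The session anchor excludes flares unrelated to a session, and no between-arm table of adverse events is announced. This stands too. What remains is that symptoms coinciding with a session cannot be attributed.

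**A condensed article omits detail.** The full protocol may say that adverse events were asked about at the interviews. That is possible, and I draw nothing from the silence on interview questions. But the definition, the source and the arm concerned are stated here, and the definition itself rules controls out.

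**Safety is not a stated objective, and risk is argued to be low.** This is fair, and it limits the weight of the point. Still, adverse events are collected and will presumably be reported for what the article describes as the first randomised trial of aqua-cycling in pre-surgical osteoarthritis.

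**Conclusion.** The point holds in a limited form. Registered non-serious and severe adverse events exist only for the aqua-cycling arm, by definition as well as by source, so their rates cannot be compared with usual care and log counts cannot separate programme effects from the disease's own variation. The both-arm diaries allow a partial comparison of knee-pain flares over about 71% of the intervention days, but none is specified. With 67 per arm and assumed flare proportions of 10% to 40%, that comparison would carry a 95% CI of about ±10 to ±17 percentage points.

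The precision figures rest on the planned sample size and assumed proportions; the statement about definitions rests on the text alone. Neither the primary outcome nor its analysis is affected. What is at stake is how any safety statement may be worded.

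**What to change.** 1. **Fix one pain-flare rule before diary data are examined by arm.** State a numeric NPRS rise above the person's own reference level (for example, their own diary median) and a minimum duration, or a rise with role restriction. Choose the threshold with clinical input. Without one, ordinary day-to-day variation would label many patients in both arms as having a flare. State how missing diary days are treated. A diary median would absorb a sustained rise in pain, so report this beside the planned comparison of pain course, not in place of it.
2. **Apply the rule identically to both arms** and report the between-arm difference with a 95% CI for months 1 and 3, stating that month 2 and weeks 13 to 24 are not covered.
3. **Report log-book events separately** as session-related and uncontrolled, and make no comparative safety claim from them.
4. **For patients who have not yet had the call before the 24-week assessment**, ask both arms the same adverse-event questions, by the same mode and not tied to a session.

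Cost: one extra analysis of data already collected and a few questions in a call already scheduled; no new visits. Limits to state: recall at the final call reaches back over the training period, the diaries are self-reported by unblinded participants, and stiffness, soreness and fatigue stay without a controlled record for most patients.

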#### Exclusion criteria

Potential participants with any contra-indication for aquatic exercise therapy such as [1] severe, unstable cardiorespiratory co-morbidities and [2] open wounds, or patients on a [3] waiting list for total knee surgery were excluded from participation in this study. Furthermore, all potential participants who met one of the following criteria were excluded given that these conditions could limit safe and full participation in the study or impede the perception of symptoms of knee OA: [4] corticosteroid injection <3 months and/or hyaluronic acid injection <6 months, [5] severe joint complaints (other than knee joint) that interfere the ability to participate in an exercise programme, [6] symptomatic and radiological apparent hip OA, [7] inflammatory joint diseases, [8] inability to safely enter and exit the pool and [9] fear of water.

Eligible patients first received verbal information by telephone. Interested patients were contacted by the programme coordinator after their consultation visit at the MUMC^+^. If their interest in participation continued after the telephone call, the programme coordinator sent additional information by mail. Each potential participant could consider participation for 1 week and was instructed to hold off any physical therapy until the randomisation results were known. If a candidate decided to participate, they had to sign an informed consent form in which they declared their voluntary participation. The programme coordinator checked incoming applications, including two short questionnaires, to screen for any contra-indications for physical activity using the physical activity readiness questionnaire (PAR-Q) and to screen for anxiety and depression using the HADS [28, 29]. In case of any doubts about a patient’s mental and/or physical health, the patient concerned was advised to contact a medical specialist for examination or advice.

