
The cool-down consisted of slowly cycling forward and backward, knee-ROM exercises and static stretching of the lower limbs to decrease the heart rate, prepare participants for the change of body position (e.g. from sitting on the exercise bike to standing position) and environment (the pool floor slowly comes up during the stretching exercises), and to reduces experienced muscle soreness.

The exercise intensity was moderate and was regulated by the patients themselves based on their perceived exertion using the BORG scale [44, 45]. In addition, heart rate is monitored by a Polar Ft 7, Wearlink® + Hybrid chest strap during each training session, and peak and average heart rates are protocolled. An average heart rate of 70-75 % of the maximum heart rate is desirable and recommended by exercise guidelines for OA [46, 47]. Furthermore, the supervising physical therapist assessed the quality of the performance by judging compensational movements, postural control, safe execution, and level of exertion (assessed by the talk test). In the event of any doubt about a participant’s health status, the physical therapist discontinued the training and referred the participant to their general practitioner.

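### The adverse-event classes cover only four musculoskeletal or fatigue complaints, so any other event that does not end in disability, hospitalization or death is recorded without a class

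*Protocol article*

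**What the plan says.** The definitions are in the protocol article under Process measures, in the paragraph on attendance, adverse events and exercise progression in the intervention group.

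- **Recording.** The therapist keeps a log book for each participant, and "adverse effects during or following the sessions were documented in the training log book". No type of event is excluded.
- **Non-serious.** "Non-serious adverse effects were defined as increased joint pain, stiffness, muscle soreness and/or fatigue occurring during or immediately after the last training session".
- **Severe.** "If these adverse events were experienced longer than 24-h or interfered with physical activities and social participation they were classified as severe adverse events".
- **Serious.** "A serious adverse event was defined as an occurrence that resulted in permanent or severe disability, hospitalization, or death".

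Two other sections bear on this. The Exclusion criteria keep out people with "severe, unstable cardiorespiratory co-morbidities and [2] open wounds", and people with "inability to safely enter and exit the pool". The Intervention group section says that, on any doubt about a participant's health, "the physical therapist discontinued the training and referred the participant to their general practitioner". It attaches no adverse-event class to such a stop.

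**The concern.** The three classes do not cover all the events that could occur in this programme. The first is a list of complaints expected from exercise, the second is a longer or more disabling form of the same complaints, and the third is reached only through a grave outcome. Between them lies a range of events that matter in a heated pool with patients who have knee osteoarthritis: falls treated without admission, dizziness, breathlessness or chest symptoms, and skin problems.

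What is at stake is the safety result. The Background and Discussion look to the trial for guidance on clinical use and for instructors of community classes. The Data monitoring section relies on a very low expected risk of adverse events to justify having no monitoring committee. If the summary is built on the stated classes, it could show few or no events of a kind that the classes cannot register, and the safety profile carried into those settings would look better than the log supports.

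**Working it through.** No sample size, rate or test enters here, and the protocol states no figure to reproduce. The check is to apply the definitions to concrete events.

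**Step 1: is the list closed?** The non-serious class is introduced as a definition and names four complaints, without any wording that marks them as examples. As written, it is closed.

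**Step 2: does the severe class widen it?** No. Its subject refers back to the events just defined. Duration over 24 hours, or interference with activities and participation, upgrades a listed complaint but does not admit a new type.

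**Step 3: does the serious class catch the rest?** Only by outcome. It accepts any type of occurrence, but only one that results in permanent or severe disability, hospitalization or death.

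**Step 4: apply the classes.**

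| Event | Logged? | Non-serious | Severe | Serious |
|---|---|---|---|---|
| Muscle soreness at the end of a session, gone the same day | Yes | Yes | No | No |
| Knee pain starting in a session and lasting two days | Yes | Listed type | Yes | No |
| Fall at the pool, outpatient treatment, no lasting disability | Can be | No | No | No |
| Dizziness or chest symptoms, session stopped, referral to the general practitioner, no admission | Can be | No | No | No |
| Skin problem after a session, no admission | Can be | No | No | No |
| Knee pain starting the next morning and lasting three days | Can be | No, onset too late | No, same list and onset | No |

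The last four rows have a place in the log and no class.

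**Step 5: the onset wording.** The recording sentence covers effects during sessions and those following them. The classifying sentence covers those during or immediately after, which is narrower. I take the last training session in that sentence to mean the most recent one. The final row of the table is thus a listed complaint, lasting more than 24 hours, that read literally still has no class. The Intervention group section also treats increased knee pain after a session as an adverse reaction when deciding on pedalling resistance, without requiring immediate onset.

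**Step 6: exposure.** 168 participants allocated 1:1 give 168 / 2 = 84 in the intervention group, and 84 × 24 = 2016 sessions at full recruitment and attendance. This is a ceiling on the number of sessions only. It does not count unclassified events, and the 168 already allows for 20 % dropout.

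**The case against.** The strongest reply is that nothing is lost. The log takes adverse effects of any type, and an open text box takes problems with exercises. Daily diaries record knee pain over two 30-day periods, and there is an interview after six weeks. A reader might infer from the definitions that an unlisted event is not an adverse event at all, or counts as zero. The documents do not support that: such an event can be recorded, and what is missing is a class for it. This part of the objection stands and limits the point to classification.

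It is also fair that no adverse-event table is described, and that tabulation may be settled in a plan not shown. The omission from a summary is therefore conditional on that summary following the stated classes. But the classes themselves are fixed in this article, and as fixed they are incomplete. The definitions cite sources that are not at hand and might show the list to be illustrative; the article's own wording does not.

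A reader might further infer that the protocol named cardiorespiratory, wound and pool-entry problems as risks of training and then failed to count them. It did not. They are pre-existing conditions used for eligibility, and eligibility conditions need not map to outcome classes. They show only that the authors thought these areas relevant to safe participation.

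Lastly, it could seem natural to treat every stopped session as an adverse event, or to count everything up to the next session. Both go too far. Training is stopped on any doubt, so some stops are precautions. With two sessions a week, a window to the next session would take in intercurrent illness, and because these events are registered only in the intervention group there would be no control rate to set against it.

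**Conclusion.** The point holds as a gap in classification. On the stated definitions, an event outside the four complaints has no class unless it ends in permanent or severe disability, hospitalization or death, and a listed complaint with later onset has none either. A safety summary that follows those definitions would omit such events and could understate harm.

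The size cannot be put in numbers, because the documents give no event rates. The conclusion rests on reading the four-item list as exhaustive, as it is worded, and on the summary using the stated classes. The primary and secondary efficacy analyses are unaffected. The matter should be corrected because the repair is cheap and the safety result is meant to inform use outside the trial.

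**What to change.** Change the reporting definitions only:

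1. Define an adverse event as any untoward medical occurrence during or following a session, whatever its type.
2. Keep the four complaints as a named subset and add an 'other' category, with falls, dizziness or syncope, cardiorespiratory symptoms and skin problems as examples.
3. Apply the grading by duration over 24 hours or interference to all recorded events, including those with later onset. Leave the serious class as it is.
4. Tabulate sessions discontinued with referral separately, and code any underlying event in its own right.
5. Re-code the existing log entries to this definition before analysis. The Trial status section says data collection was still ongoing, so this can be done in time.

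The cost is a change of wording and one re-reading and coding of the training logs. Reported counts will be higher, and re-coding can recover only what the therapists wrote down, which the report should say.
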